### Randomisation

After data collection, schools will be randomly allocated to control (*n* = 9) or intervention (*n* = 9). Randomisation will be stratified by country and random allocation will be performed by faculty staff who will be blind to school identity and independent of the study team.

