## Methods

### Study design

The WISH study is a school-based clustered randomised controlled trial (c-RCT). The design of the project was informed by a feasibility pilot study [50] that used the Medical Research Council (MRC) [51] framework for complex interventions to develop a peer-led walking intervention. Specifically, following a systematic review of walking interventions in children and adolescents [31], focus groups were conducted to explore the attitudes of adolescents towards physical activity [37]. The findings of both the systematic review and focus groups were used to inform the design of the peer-led, school-based walking intervention [50] based on the socioecological framework and informed by Self-Determination Theory (SDT), which provides a framework for understanding and enhancing the motivational mediators of behaviour change [52–54].

Eighteen post-primary schools will be recruited across the Border Region of Ireland / Northern Ireland. Following completion of baseline data collection, schools will be randomised using a 1:1 allocation. Study outcomes will be assessed at four timepoints: baseline (T0), mid-intervention (T1), end of intervention (T2) and follow up (T3) as outlined in Fig. 1. A mixed-methods process evaluation will be undertaken at baseline and at the end of the intervention. Table 1 provides an overview of data collection and outcome measures, the details of which are provided below.

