### Recruitment

#### School recruitment

The study setting will be post-primary schools in the Border Region of Ireland / Northern Ireland. Using school enrolment data [68, 69], schools that meet the following criteria will be invited to participate:
Northern Ireland: Schools that have at least 80 girls across years 9–10 and located in Co. Derry/LondonderryIreland: Schools in Co. Donegal with an enrolment of > 240 girls

Invitation letters accompanied with an expression of interest form will be sent to school principals. Where requested, a member of the research team will visit the school to provide a short overview of the trial for relevant staff. We aim to recruit 18 schools, of which 9 will be randomly allocated to intervention arm with the other 9 allocated to the control arm. Within each school, at least 24 children will be recruited (i.e., minimum of 432 children in total). Should it not be possible to recruit eighteen schools in the selected counties, schools that meet the inclusion criteria (Northern Ireland: at least 80 girls across years 9–10; Ireland: enrolment of > 240 girls) from other counties across the Border Region of Ireland / Northern Ireland will be invited to participate.

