#### Secondary outcomes

As outlined in Table 1, a number of secondary outcomes will also be assessed. It is also important to note, however, that there are no statistical power calculations for these assessments and as such all analyses will be presented with point estimates and 95% confidence intervals but without *p*-values. Accelerometer data will be used to calculate:
Total physical activity (counts per minute) at mid-intervention (T1) and follow up (T3)Time spent in sedentary behaviour and light, moderate and vigorous intensity physical activity [74] at mid-intervention (T1), end of intervention (T2) and follow up (T3)Proportion of pupils meeting current physical activity recommendations [6] at mid-intervention (T1), end of intervention (T2) and follow up (T3)

The following secondary outcomes will be measured at baseline (T0), end of intervention (T2) and follow up (T3) to assess between group differences and changes over time:

Height (cm) and weight (kg) will be measured to the nearest 0.1 cm and 0.1 kg, respectively, using a freestanding stadiometer (Leicester Height Measure), and digital scales (Seca 877) to calculate body Mass Index (BMI). BMI will be converted to an age-specific and gender-specific z-score [75, 76]Waist and hip circumference will be measured to the nearest 0.1 cm using an anatomical measuring tape and waist-to-hip ratio will be calculated.Coping, resilience and cognitive reappraisal [55]Sleep quality, duration and efficiency (The Pittsburgh Sleep Quality Index) [56]Social media use, social integration and emotional connection to social media [57, 58]Body weight and appearance satisfaction [59]

At baseline (T0) the following descriptive data will be collected:
Date of birthHome postcode/Eircode to derive Index of Multiple Deprivation (IMD)

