#### Quantitative analysis

Outcome data will be reported in accordance with Consolidated Standards of Reporting Trials (CONSORT) guidelines [78]. The statistician performing the data analyses ([name]) will be blinded to allocation throughout the study and statistical analysis will only be undertaken when all data has been collected (T3). Pupils will be included in the analysis regardless of compliance with the physical activity intervention. We will apply a multilevel statistical model using ML- win [79] to assess changes in total physical activity (mins per week) from baseline to post-intervention. Multilevel modelling will also be used for the change in total physical activity at other timepoints and secondary continuous outcomes adjusting the false discovery rate using the Benjamini-Hochberg Procedure [80]. Outcomes will be compared between the control and intervention groups using a 2-level multilevel model, with pupils nested within schools. The models will be adjusted for the child-level covariates (level 1): baseline total physical activity (minutes per week), age and BMI z-score; and the following school-level covariates (level 2): social economic status (postcode/Eircode). In the interests of parsimony, covariates will only be retained if their inclusion results in a significant improvement in fit statistics.

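### School randomisation is stratified by country, but the listed analysis model omits country and its retention rule could drop it even if added

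*Protocol article*

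**What the plan says.** Under Study design, "schools will be randomised using a 1:1 allocation". School recruitment gives the numbers: "We aim to recruit 18 schools, of which 9 will be randomly allocated to intervention arm with the other 9 allocated to the control arm". The Randomisation section adds the only stratification factor: "Randomisation will be stratified by country".

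Under Quantitative analysis, "Outcomes will be compared between the control and intervention groups using a 2-level multilevel model, with pupils nested within schools". The pupil-level covariates are "baseline total physical activity (minutes per week), age and BMI z-score". The school-level entry is "the following school-level covariates (level 2): social economic status (postcode/Eircode") and nothing else. A selection rule follows: "covariates will only be retained if their inclusion results in a significant improvement in fit statistics".

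Country is neither a covariate nor a level of the model. The article gives no reason for leaving it out and does not adjust for it anywhere else.

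**The concern.** Stratifying by country balances the two countries across arms, so the treatment contrast does not carry the country difference. The analysis benefits from this only if the model knows about country. If it does not, any remaining country difference stays in the school-level residual. The reported standard error then exceeds the true sampling variability of the estimate, intervals are too wide, and the test rejects a true null less often than 5%.

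This is not a detail left for a later document. The article lists the covariates and fixes the rule for keeping them. That rule is also unsuitable for a stratification factor: country belongs in the model because of how schools were allocated, not because a fit statistic favours it in a sample of 18 schools.

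At stake are some power for the primary outcome and the width of the intervals for secondary outcomes. The article reports secondary outcomes by estimate and 95% interval without p-values, so the interval is the main result there.

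**Working it through.** **Inputs from the article (Sample size calculations, School recruitment).** Difference 11.41 min/day; SD 25; power 80%; alpha 0.05 (two-sided assumed); mean cluster size m = 20; ICC 0.03; coefficient of variation (CV) of cluster size 0.46; 18 schools to be recruited.

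**Assumptions.** The between-country difference D is not given and is varied. Schools are split equally between countries with balanced arms. The scale is min/day, as in the sample size section.

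**1. The plan's own figure.**
- Per arm, unclustered: 2 × (1.960 + 0.842)² × 625 / 11.41² = 75.4.
- Design effect: 1 + ((0.46² + 1) × 20 − 1) × 0.03 = 1.697.
- Pupils per arm: 75.4 × 1.697 = 127.9, which is 6.39 schools per arm or 12.8 in total.
- Adding one school per arm gives 14.8, so 15. A t test on 13 degrees of freedom with 15 schools gives 80.1% power.

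The stated 15 schools therefore reproduce.

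**2. Country included, 18 schools, no baseline adjustment.**
- Variance of a school mean: v = 625 × 1.697 / 20 = 53.03.
- SE = √(4 × 53.03 / 18) = 3.43.
- Power by noncentral t on 15 df: 87.4%, whatever the value of D.

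**3. Country omitted.** The expected residual variance becomes v + (D²/4) × 18/16, because the country contrast is left in a residual with 16 df.
- D = 5: 53.03 + 6.25 × 1.125 = 60.06, so the reported SE is √(4 × 60.06 / 18) = 3.65 (+6%).
- D = 10: 53.03 + 25 × 1.125 = 81.16, so the reported SE is √(4 × 81.16 / 18) = 4.25 (+24%).

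The true SE of the estimate remains 3.43. Simulated power and type I error:

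| D (min/day) | Reported SE, omitted | Power, omitted | Power, included | Type I error, omitted |
|---|---|---|---|---|
| 0 | 3.43 | 87.7% | 87.4% | 5.0% |
| 5 | 3.65 | 84.7% | 87.4% | 3.8% |
| 7.5 | 3.91 | 80.8% | 87.4% | 2.7% |
| 10 | 4.25 | 75.0% | 87.4% | 1.7% |

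**4. With the baseline covariate the article specifies.** Assume a baseline correlation of 0.6, the same D at baseline and follow-up, a 10/8 country split and equal cluster sizes.
- Design effect 1 + 19 × 0.03 = 1.57, so v = 625 × 1.57 / 20 = 49.06.
- After adjustment, school-mean variance is 49.06 × (1 − 0.36) = 31.40, and a 10-minute difference shrinks to 10 × (1 − 0.6) = 4 minutes.
- Omitted: 31.40 + 16 × (10 × 8 / 18) / 16 = 35.84, reported SE 2.82. Included: SE √(4 × 31.40 / 18) = 2.64. The excess is 7%.
- Simulated power, omitted against included: 98.1% and 98.2% at D = 5; 97.2% and 98.0% at D = 10; 96.4% and 98.0% at D = 15. Type I error with country omitted: 4.5%, 3.8% and 2.7%.

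**5. A weaker baseline correlation.** With 16 schools, CV 0.46 and correlation 0.4, power omitted against included is 85.9% and 87.8% at 0.3 SD (7.5 min), and 80.8% and 87.6% at 0.5 SD (12.5 min).

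**6. A possible ceiling on D.** Between-school variance at ICC 0.03 is 0.03 × 625 = 18.75. If the pilot ICC already spans both countries, D²/4 cannot exceed 18.75 for an equal split, so D is at most 2 × √18.75 = 8.7 min. The article does not say whether it does.

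**The case against.** The best defence is that the primary model adjusts for baseline activity. A stable country difference is largely present at baseline, so the adjustment removes much of it. This stands, and it makes the primary-outcome loss small under the assumptions in step 4. For small residual differences, the loss is nil or offset by the degree of freedom saved.

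Three further points also stand. The error is conservative: no bias and no inflated type I error. The trial plans 18 schools against 15 required, so even the unadjusted calculation stays above 80% at a 7.5-minute difference. And if the pilot ICC covers both countries, the omission forgoes a gain rather than pushing power below plan.

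The defence covers less for secondary outcomes. The listed baseline covariate is total physical activity, not each outcome's own baseline. For sleep, social media use or body satisfaction it may absorb little of a country difference.

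A reader might infer more than the documents support in three ways:
- **That the primary analysis is underpowered.** The 75.0% figure comes from a model without the baseline covariate that the article specifies, at a difference the article does not give.
- **That school-level variance dominates precision.** In SD² units, the article's inputs give a school component of 0.03 against a pupil component of 0.97/20 = 0.0485 in a school mean.
- **That deprivation is entered at the wrong level.** The article collects home "postcode/Eircode to derive Index of Multiple Deprivation (IMD") and lists socio-economic status at school level. A school mean of pupils' deprivation, or the school's own postcode, would be a legitimate school-level covariate, so no error is established.

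**Conclusion.** The point holds as a modest defect of efficiency and calibration. The sole stratification factor is missing from a fully listed model, and the retention rule would not protect it. If the countries differ appreciably after adjustment, intervals are too wide and the test is conservative.

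For the primary outcome the likely cost is small: under 1 point of power at a 10-minute difference with baseline correlation 0.6, and about 2 points at 7.5 minutes with correlation 0.4 and 16 schools. It approaches the unadjusted figures only if baseline activity explains little of the country difference. That is more plausible for some secondary outcomes, whose intra-class correlations and country differences the article does not give. Every size quoted rests on an assumed country difference and, where adjusted, an assumed correlation. The sample size is unaffected.

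**What to change.** Add country (Northern Ireland or Ireland) as a fixed effect in the primary model and all secondary models, and state that it is kept regardless of the fit-statistic rule. This takes one or two sentences in the analysis section.

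The cost is one school-level degree of freedom. If the countries do not differ, power falls by about 0.3 points with 18 schools (87.7% to 87.4%), or about 1 point in a 16-school simulation (83% to 82%). No extra data are needed, because each school's country is known at randomisation.

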### Intervention

Female pupils aged 15–18 years (peer role models) with few existing extra-curricular commitments within school will be identified by school staff and invited to train as walk leaders to lead younger pupils (aged 12–14 years) in 10–15-min walks before school and at break and lunch recess (maximum 15 walks per week (3 per day)). All walks will occur in school grounds and pupils will be encouraged to participate in many walks as possible each week. Walks will primarily take place outdoors but in adverse weather conditions, indoor routes will be used where possible. Each pupil will be issued with a reward card which will be stamped after each completed walk. These cards will allow pupils to self-monitor their attendance, and stamps can be exchanged for small rewards with low monetary value (<€1), for example, pens, pencils, rulers.

The training for walk leaders has been developed in consultation with the Physical Activity Co-Ordinator (Western Health and Social Care Trust) and is based on the *Walking For Health* Training (Public Health Agency & NI Health and Social Care Trusts). The training aims to provide an overview of the WISH Study, an understanding of health walks, the expectations of WISH Walk Leaders, knowledge of how to plan walks and keep walkers motivated. The training will also inform walk leaders of the support available for them in this role. Training will be delivered by the Trial Manager on school premises and will last approximately 3 h. The training session has been divided into five sections: 1) completion of consent forms and study questionnaires; 2) ice breakers; 3) presentation and group work to focus on ensuring walk leaders consider safety concerns of facilitating the walks and the importance of the walks being performed at a brisk pace, i.e. at a pace sufficient to elicit moderate intensity physical activity in pupils. Training will also include information on providing and encouraging social support amongst pupils to align with SDT; 4) Walk leaders will be provided with instructions on how to plan walk routes (agreed by teachers) and they will also draft the walking timetable and arrange a central meeting point; 5) Walk leaders will have the opportunity to practice leading a walk under the supervision of the Trial Manager. All walk leaders and will be provided with a training manual and asked to evaluate the training programme. Refresher training will be available throughout the intervention. Should a school arrange refresher training, this will last approximately 1 h and focus on the pace of the walk, encouraging social support and planning new/alternative walking routes. During the refresher training, walk leaders will have the opportunity to practice leading a walk and they will be provided with feedback on pace, route and social engagement. The walk leader training is theoretically underpinned by SDT and similar to the Bristol Girls Dance Project [70], the training facilitator will adopt an autonomy-supportive teaching style that strengthens walk leaders’ personal resources. Walk leaders will be encouraged to decide the format of the walks for example, the use of music or games and routes taken. They can also choose to introduce themed walks (for example, Santa walks at Christmas). Walk leaders will be able to self-select the walks that they would like to lead, and the timetable will be determined based on the preferences of the walk leaders. Within a supportive training environment, walk leaders will be provided with the skills and competence to run the walking programme within their school.

Two walk leaders will accompany each walk, one at the front and one at the back of the group. If possible, a third walk leader will be present in the middle of the group. Walk leaders will encourage the younger pupils, set the pace of the walk and ensure the safety of pupils. Walk leaders will be provided with wrist worn heart rate monitors (Mi Band 3, Xiaomi, China) to guide the pace of the walk. Walk leaders will be advised to check that their heart rate is > 135 bpm which indicates that they are walking at a brisk pace [71]. Walk leaders will also be trained to look out for other signs that they are walking at a brisk pace (breathing a little faster; feeling a little warmer; feel their heart beating a little faster; still able to hold a conversation) should they choose not to wear the heart rate monitor. The walk leaders will monitor the pace of the walk and regularly remind pupils that they should be walking at a brisk pace and although there will be variations in fitness and perceived effort, this is reflective of a walking group. For most pupils, walking at the same pace as the walk leaders will be of moderate intensity. Walks will take place in a one of the pre-planned routes around the school grounds. At the end of each walk, walk leaders will stamp each pupils reward card and note attendees to monitor compliance with the intervention. Pupils who are not enrolled in the study are permitted to join the walks and will be provided with a reward card which they can exchange for small value rewards. Risk assessments will be performed by a member of the research team and a member of school staff for each predetermined walking route.

Following baseline measurements, the intervention will be delivered for the whole school year. Allowing for holidays, exams, educational trips and other school events this may vary across schools however the intervention will be a minimum 20 and a maximum of 22 weeks. As part of the social support component of the intervention, walk leaders will be invited to be part of a separate closed social media (Facebook) group designed to include opportunities for social support in the form of sharing progress and useful information. In addition, social support and encouragement to continue will be provided to walk leaders via weekly updates from the research team which will include: strategies to address barriers to participation, recognising progress; links to websites and resources; and vignettes of support and advice from other walk leaders. These pages will only be accessible to those in the intervention and will be moderated by named members of the research team for data protection.

### Outcomes

#### Primary outcome

The primary outcome will be total physical activity (counts per minute) of pupils at the end of the intervention (T2) measured using the Actigraph GT3X accelerometer (Actigraph LLC, Florida) worn for 7 days. The device will be placed on an elastic waist band and pupils will be asked to wear the accelerometer at all times, removing it only for bathing, water-based activities such as swimming and when asleep. Pupils will be asked to wear the accelerometer on their right hip and to ensure that it is worn in the same position each day. Pupils will be asked to wear the accelerometer for seven consecutive days and will be included in the analysis if they have ≥2 valid weekdays of data (500 mins/day) [72]. During measurement periods, pupils will be asked to keep a log of when they wore the accelerometer and took it off to encourage compliance with the wear-time protocol as recommended by Trost et al, 2005 [73]. Minutes of total physical activity (light, moderate and vigorous) per day will be estimated using the Evenson cut-points [74]. A sampling epoch of 15 s will be employed during data collection. Periods of ≥60 min of zero counts will be categorised as ‘non-wear’ and removed.

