**Methods:**

The Walking In ScHools (WISH) Study is a school-based c-RCT conducted with girls aged 12–14 years from eighteen schools across the Border Region of Ireland / Northern Ireland. Following baseline data collection, schools will be randomly allocated to intervention or control group. In intervention schools, female pupils aged 15–18 years will be invited to train as walk leaders and will lead younger pupils in 10–15 min walks before school, at break and lunch recess. All walks will take place in school grounds and pupils will be encouraged to participate in as many walks as possible each week. The intervention will be delivered for the whole school year (minimum 20–22 weeks). The primary outcome measure is accelerometer-measured total physical activity (counts per minute) (end of intervention). Secondary outcomes will include time spent in sedentary behaviour, light, moderate and vigorous intensity physical activity, anthropometry measures, social media usage and sleep. A mixed-methods process evaluation will also be undertaken.

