### Sample size calculations

Sample size calculations are based on the WISH feasibility trial [50], which detected a mean difference of 11.41 min in total physical activity (light, moderate and vigorous intensity physical activity) measured using accelerometery between the intervention (2 schools consisting of a total of 79 children) and control (4 schools consisting of 84 children in total) groups. In order to detect a difference of 11.41 min total physical activity per day between groups, assuming a standard deviation (SD) (pooled intervention and control group SD) of 25 min in total physical activity, a power of 80%, a significance of 0.05, an average cluster size of 20 children, an intra-class correlation of 0.03 (calculated from pilot data [50]), and a coefficient of variation of 0.46, the sample size needed is 15 schools increasing to 16 schools (8 per study arm) to allow for 10% cluster attrition. To allow for 20% loss to follow up we will recruit at least 24 children per cluster (at least 384 children in total). Based on recruitment rates of 34% in our feasibility study [50], all schools that have at least 80 girls across years 9–10 (Northern Ireland) or total enrolment of > 240 girls (Ireland) will be eligible to participate in the study. From the Northern Ireland School Census [68] we estimate that 77 schools meet these criteria and based on 2016 school recruitment data for Ireland [69] 54 post-primary schools meet these criteria.

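### The declared primary outcome (counts per minute) is not the variable that was powered or the one named in the primary model (minutes of activity), so its power is unknown

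*Protocol article*

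**What the plan says.** The article describes total physical activity in different ways in different sections.

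- **Outcome declaration.** The abstract (Methods) states: "The primary outcome measure is accelerometer-measured total physical activity (counts per minute) (end of intervention"). The Primary outcome section agrees: "The primary outcome will be total physical activity (counts per minute) of pupils at the end of the intervention (T2"). Secondary outcomes uses counts per minute again for T1 and T3.
- **A second variable, also derived.** Later in the Primary outcome section: "Minutes of total physical activity (light, moderate and vigorous) per day will be estimated using the Evenson cut-points". This is time spent above a threshold.
- **Sample size calculations.** The target is in minutes: "In order to detect a difference of 11.41 min total physical activity per day between groups". The pooled SD is taken as 25 min, with 80% power, a 0.05 significance level and 20 pupils per school on average. The ICC of 0.03 comes from the pilot, and a coefficient of variation of 0.46 is added.
- **Quantitative analysis.** The multilevel model is to be used "to assess changes in total physical activity (mins per week) from baseline to post-intervention", and the child-level covariates are "baseline total physical activity (minutes per week), age and BMI z-score".

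No section gives a difference, SD or ICC for counts per minute, or says that counts per minute and minutes may stand in for each other.

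**The concern.** Counts per minute averages the accelerometer signal over wear time, so it weights activity by intensity. Minutes of total activity count every minute above the sedentary cut-point equally. No constant turns one into the other, so the standardised effect and the ICC can differ between them.

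This intervention makes the difference practical. The walks are meant to be brisk and of moderate intensity. If brisk walking replaces sitting, which is the trial's hypothesis, both measures rise. If it replaces light activity such as strolling at recess, counts per minute rises while total light, moderate and vigorous minutes stay the same. The two measures could therefore give different answers.

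The primary comparison carries the confirmatory claim, because the Secondary outcomes section reports secondary results without p-values. With the declaration in one variable and the power and model in another, the article does not settle which comparison that is. The Discussion's claim that the trial is fully powered also lacks a basis for the declared outcome.

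**Working it through.** **1. Reproduce the stated 15 schools (minutes per day).**

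Inputs from Sample size calculations: difference 11.41 min, SD 25 min, power 80%, significance 0.05 (sidedness not stated; two-sided assumed), mean cluster size m = 20, ICC 0.03, CV 0.46 (read as the CV of cluster size).

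- Standardised effect: 11.41 / 25 = 0.456.
- Design effect: 1 + ((1 + CV²)·m − 1)·ICC = 1 + ((1 + 0.46²)·20 − 1)·0.03 = 1.697.
- 15 schools: 7.5 × 20 = 150 pupils per arm on average. Effective number: 150 / 1.697 = 88.4 per arm.
- Noncentrality: 0.4564 × √(88.4 / 2) = 3.03. Critical t on 15 − 2 = 13 df: 2.160.
- Power from the noncentral t: 0.801. With 14 schools it is 0.768.

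Fifteen schools is therefore the smallest number that reaches 80%. The plan's calculation is correct for minutes per day.

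**2. Day against week.**

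If a week is seven times a day, the target is 11.41 × 7 = 79.87 min and the SD is 25 × 7 = 175 min. The ratio is again 0.456, so power stays at 0.801. With five days, 57.05 / 125 gives the same ratio. This part of the mismatch does not affect power. How a weekly total is formed for a pupil with only two valid weekdays would still need a rule.

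**3. Minutes against counts per minute.**

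No power can be computed for counts per minute from the article, because all three inputs are absent. What can be shown is how power depends on the unknown standardised effect. *Assumptions:* 18 schools (9 per arm), 24 × 0.8 = 19.2 analysed pupils per school, CV 0.46, t on 16 df, no gain from baseline adjustment and no loss of whole schools.

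- Design effect at ICC 0.03: 1 + ((1 + 0.46²)·19.2 − 1)·0.03 = 1.668.
- Effective number per arm: 9 × 19.2 / 1.668 = 103.6.
- Noncentrality: effect × √(103.6 / 2). Critical t: 2.120.

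| Assumed effect on counts per minute (SD) | Power, ICC 0.03 | Power, ICC 0.05 |
|---|---|---|
| 0.30 | 53% | 44% |
| 0.35 | 66% | 56% |
| 0.40 | 77% | 67% |
| 0.456 | 87% | 78% |
| 0.50 | 92% | 85% |

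At ICC 0.03, the 80% is kept with 18 schools if the effect on counts per minute is at least about 0.41 SD. Nothing in the article says on which side of that value the effect lies.

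**The case against.** **It is a drafting slip.** Both places that declare the primary outcome say counts per minute at T2. The analysis section also has a sentence without a unit, under which outcomes are compared in a two-level model, and this could cover counts per minute. The same section refers to total physical activity at other timepoints, which Secondary outcomes defines in counts per minute. This stands in part: it would be too strong to infer that no model will be fitted to the declared outcome. But the only unit named for the primary model is minutes, and it appears for both the response and the baseline covariate, so the text does need correcting.

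**There are not three competing outcomes.** This stands. Day and week are the same test if the week is a fixed multiple of the day.

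**A reader might infer that the sponsor is free to pick the outcome after seeing results.** The documents do not support so strong a reading. Counts per minute is declared consistently, the analyst is blinded, and analysis waits until T3. A switch to minutes would visibly depart from the declaration. Some room remains, because the sample size and analysis sections could be cited in its defence.

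**The powered variable is not ignored.** Minutes of total activity per day are derived, and time in light, moderate and vigorous activity is a secondary outcome at T2. Only the total is not named as one.

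**A reader might infer that the trial is underpowered.** The documents do not show this. An outcome that weights intensity could respond more strongly to brisk walking, and baseline adjustment could raise power. Loss of whole schools would lower it.

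**Conclusion.** The inconsistency is real and lies in the current text. It is a contradiction between sections, not a detail left to an analysis plan. The declared primary outcome is neither the variable powered nor the one whose unit the primary model names. The substantive conflict is between two variables, counts per minute and minutes of activity.

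The arithmetic for minutes per day is sound. For counts per minute, the stated 80% and the fully powered claim are unsupported, and its power is unknown. The span of 53% to 92% at ICC 0.03 only illustrates that uncertainty: it rests on assumed effects of 0.30 to 0.50 SD, with the ICC and CV carried over from the minutes calculation. It should be corrected, because it determines what the trial's main comparison tests.

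**What to change.** Before any T2 data are seen, use one variable in the abstract, Sample size calculations, Primary outcome, Secondary outcomes and Quantitative analysis.

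- **If counts per minute stays primary:** change Quantitative analysis to model counts per minute at T2, adjusted for baseline counts per minute. Restate the sample size section with a difference, SD and ICC for counts per minute and the power that 18 schools give. The pilot may supply these inputs, but the article reports only minutes from it. If they are not available, say that the 80% applies to minutes per day only. Name total minutes per day as a secondary outcome.
- **Otherwise:** make minutes per day primary in all of these sections. The existing calculation then applies to the primary outcome.

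The cost is wording and, under the first option, one recalculation. The stated power may become less favourable.
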